## Abstract

**Background:**

Lung cancer is one of the most common cancers in Germany, with around 56,000 new cases diagnosed in 2020. Approximately 65% are diagnosed at advanced stages, where symptoms such as fatigue, pain, dyspnea, and weight loss are prevalent. These patients often suffer from cardiovascular and pulmonary comorbidities, which interact with treatment toxicity, outcome, and increase treatment costs. Although exercise therapy is proven to alleviate cancer-related symptoms and to improve quality of life, current lung cancer treatment guidelines fail to adequately prioritize its crucial role.

**Methods:**

The Better symptom contRol with Exercise in pAtients wiTH advanced non-small cell lung cancer (BREATH) study is a prospective, three-arm randomized controlled trial (RCT) designed to assess the impact of exercise therapy on patients with advanced NSCLC (stage IIIB-IV) who are receiving first- or second-line systemic therapy in the palliative setting. Patients (*n* = 104) are randomized in a 2:1:1 ratio into a control group (receiving exercise recommendations) or one of two intervention arms: endurance training and breathing exercise or combined endurance and resistance training. The intervention groups will exercise twice a week for 12 weeks. The control group participants will be randomized again in a 1:1 ratio into one of the two intervention arms after completion of the control period. The study will assess outcomes at baseline, 12 weeks, and 24 weeks. The primary outcome is improvement of aerobic capacity (VO_2_ peak). Secondary outcomes include quality of life, fatigue, adherence to exercise, and adverse events. Patient representatives were involved in all stages of protocol development.

**Discussion:**

The BREATH study addresses a significant gap in the current management of advanced lung cancer treatment by evaluating the impact of different exercise treatment protocols to reduce symptoms and improve clinical outcome. The study design and exercise program aim to enhance adherence and optimize patient-related outcomes. The results of the BREATH study have the potential to influence future guidelines and improve the management of patients with advanced NSCLC.

**Trial registration:**

ClinicalTrials.gov NCT06374160. Registered on April 18, 2024.

## Background

With approximately 56,000 new cases in 2020, lung cancer is one of the most common cancer entities in Germany [1]. Approximately 65% are diagnosed in advanced stages [2–4]. Prominent symptoms during the cancer trajectory include tumor-related fatigue [5, 6], pain [7], depression [8], cough [9], dyspnea (shortness of breath) [10], weight loss/appetite loss [11], and sleep problems [12, 13]. In addition to these cancer-related symptoms, patients with advanced lung cancer typically present with comorbidities, with the common causal root in nicotine consumption. Cardiovascular diseases and chronic obstructive pulmonary disease (COPD) form the most common and relevant comorbidities [14]. Besides a significantly adverse effect on treatment outcome [15], patients with multiple comorbid conditions require more outpatient and inpatient treatments, leading to higher treatment costs [16, 17]. To support these multimorbid patients, multimodal strategies need to be developed. The Roundtable Report of the American College of Sports Medicine recommends that cancer patients engage in moderate physical activity for 150–300 min per week [18]. However, in the current German S3 guidelines for the diagnosis and treatment of lung cancer, exercise interventions are only marginally addressed [2], and in the real-world setting, oncologists rarely recommend exercise [19]. Additionally, many barriers exist for patients to self-implement exercise as a routine. Over 700 studies involving 50,000 cancer patients have evaluated the impact of exercise therapy in oncological patients [20]. Exercise therapy demonstrates improvements in cancer-related side effects such as fatigue, pain, quality of life [21], dyspnea [22–24], cardiologic performance [25] or physical fitness, and prevents muscle loss during active systematic treatment [26–31]. In addition to improving cancer-specific symptoms, exercise therapy interventions show a positive impact on patients with COPD or cardiovascular disease [32–34]. Since comorbidities have been proven to worsen the quality of life and prognosis of therapy, exercise therapy can offer relief from symptom burden in addition to oncological systematic therapy [35–37]. Advanced metastatic lung cancer patients exhibit a significantly increased symptom burden along with a low quality of life compared to other tumor entities [38]. The feasibility of exercise and potential barriers in patients with advanced cancer have been studied in recent years [39–41]. Published exercise studies specifically targeting patients with advanced lung cancer have limited evidence: sample sizes in clinical trials were insufficient to evaluate the effect of exercise therapy. Almost all randomized controlled trials included fewer than 50 subjects [42–55]. Recruitment rates range from 25 to 70%, with significantly higher dropout rates (15–42%) compared to other patient cohorts with advanced tumor diseases. Only half of the published studies report the rate of adherence to the exercise intervention.

First-line treatment of metastatic non-small lung cancer (NSCLC) is molecularly stratified. After molecular diagnostics, eligible patients (EGFR, ALK, ROS1, RET) receive targeted treatment, while the majority of patients receive (chemo)immunotherapy. Standard-of-care platinum-based chemo-immunotherapy typically consists of four cycles of platinum-containing chemotherapy combined with immunotherapy, followed by immunotherapy maintenance. The addition of immunotherapy in the last decade led to a significant improvement, with 5-year overall survival rates of 20%, or 30% in selected subgroups [56, 57]. Despite this improvement in therapy, there are currently no studies combining standard-of-care immunotherapy-based systemic therapy for advanced lung tumors with exercise intervention. Of note, immune checkpoint inhibitors (ICI) targeting programmed cell death protein 1 (PD-1), programmed cell death protein ligand 1 (PD-L1), or cytotoxic T-lymphocyte-associated protein 4 (CTLA-4) have the potential to induce rare but severe toxicity such as pneumonitis, hepatitis or ICI-related myocarditis, heart failure and arrhythmias, other various cardiologic diseases, or major cardiac events (MACE) [37, 58–63]. Initial preclinical studies show a positive synergistic effect between exercise therapy and immunotherapy [64–68]. Considering the current literature, it is evident that a successful exercise therapy concept has not yet been implemented for advanced lung cancer patients.

### Objectives

The primary objective is to achieve an improvement in aerobic capacity (VO_2_ peak) from t0 to t1 through exercise therapy compared to the standard of care. As a secondary objective, we aim to examine whether there is a difference between the two exercise therapies regarding the performance improvement (VO_2_ peak) from the beginning of the therapy to the end of the therapy (either t2 compared to t1 or t1 compared to t0, depending on the randomization arm). Other secondary objectives are to assess changes in quality of life, fatigue, dyspnea during the study participation and evaluation adherence to the intervention, dropout rates, adverse events, and tumor therapy response.

## Methods and design

BREATH is a prospective 3-arm randomized controlled trial (RCT) including histologically confirmed advanced NSCLC (UICC stages IIIB, IIIC, and IV) patients during palliative anti-cancer treatment. Patients in stage IIIB and IIIC will only be enrolled if potentially curative treatment options were excluded. Enrollment started in June 2024 and is estimated to be open for 2.5 years (Fig. 1). Study participants will be divided into study arms using a 2:1:1 randomization, with one control group and two exercise therapy groups. Participants in the two intervention arms will undergo exercise therapy, with one group receiving individual endurance training with additional breathing exercise and the other group receiving a combination of endurance and resistance training. Both intervention groups will exercise supervised twice a week for 12 weeks. The control group will initially undergo standard of care for 12 weeks. Afterwards, the patients in the control group will be randomized into one of the two intervention arms and will also receive treatment twice a week for 12 weeks. This approach has the advantage of providing a sufficiently large sample for both comparing overall exercise therapy with the control group and comparing the two types of exercise therapy. In addition, this design allows all participating patients to receive exercise therapy. By individually measuring the hypothetical one-repetition maximum (h1-RM) and conducting cardiopulmonary exercise testing (CPET) on a cycle ergometer, a tailored individual training program based on current performance will be offered to the patient. BREATH exercise begins with moderate exertion and is progressively increased during the course of the study participation (see Interventions for a detailed description). Outcome measurement will be at baseline (t_0_), after 12 weeks (t_1_), and after 24 weeks (t_2_), leading to a maximum study participation of 6 months (Fig. 1). The Ethics Committee of the Medical Faculty University of Duisburg-Essen approved this study (22–10522-BO) in December 2023 (Table 1).

**Fig. 1 Fig1:**
[figure not shown]
Study design of the BREATH study

**Table 1 Tab1:** Inclusion criteria of the BREATH study

Inclusion criteria	Exclusion criteria
• Patients with histologically confirmed non-small cell lung carcinoma in UICC stages IIIB, IIIC, and IV • First- or second-line therapy (inclusion up to 28 days after the first cycle) in palliative intention • Age ≥ 18 years • Signed informed consent	• Severe cardiopulmonary disease (EF < 30%) • Newly occurring or progressive uncontrolled CNS (central nervous system) metastases • Expected life expectancy < 3 months • Bone metastases with acute risk of fracture • ECOG (Eastern Cooperative Oncology Group) performance status > 2 • Acute pulmonary embolism • Acute myocardial infarction • Requiring surgery for aortic aneurysm • Tension pneumothorax • Lack of proficiency in the German language • Active infection

Patients with NSCLC at the West German Cancer Center (University Hospital Essen and University Medicine Essen—Ruhrlandklinik) will be identified by the treating physicians, specialist nurses, by screening patients presented at the multidisciplinary tumor board, or by systematically screening patients receiving routine follow-up scans during first-line treatment. Furthermore, patients will be recruited through clinic posters, study flyers, and direct outreach during visits to local lung cancer self-help groups. Informed consent will be obtained by the treating physician. After study inclusion, exercise assessment (baseline) followed by randomization will be performed. Intervention will be delivered by exercise scientists with a special qualification in oncological exercise therapy.

Slow recruitment will be addressed by intensifying on-site outreach (additional posters/flyers, repeated visits to the self-help group, and regular reminders to treating physicians).

### Participant retention and follow-up

Unless patients withdraw consent entirely, we will continue to invite them to all scheduled assessments and collect the primary outcome (VO_2_ peak at 12 weeks and 24 weeks) and secondary outcomes (patient-reported outcomes). Data collected up to the point of discontinuation or death will be retained for ITT and PP analyses.

### Variables and data collection

The full variables of the BREATH study are displayed in Table 2. Anthropometric and medical data includes the following variables: age, weight, highest education, marital status, date of first cancer diagnosis, tumor diagnosis, tumor stage, TNM classification, first-line or second-line treatment, histology, metastasis and location, PD-L1 expression, and molecular pathology based on sequence analyses.

**Table 2 Tab2:**
[figure not shown]
Spirit figure of the trial data collection points

^1^Check Table 1 for inclusion criteria

^2^Allocation to intervention groups will be done after completion of baseline assessment. Following randomization, strata will be used: 1. Histological stratification (non-squamous vs. squamous) and 2. Forced expiratory volume in 1 s (FEV1) >50 and under <50

^3^Randomization of the control group based on the same strata used for the first randomization

^4^Blood sampling will be done at every visit for anti-cancer treatment mostly every 3 weeks until the study ends. Cisplatin-based treatments 1 + 8 day followed by 3 weeks. Carboplatin and docetaxel d1 q3w. Blood sampling consists of BNP, high-sensitive troponin T/I as heart markers, hemoglobin [g/dl], erythrocytes [count/pl], leukocytes [count/nl], lymphocytes [count/nl], neutrophils [count/nl], C-reactive protein [mg/dl], and cytokeratin-19 fragment, CYFRA 21-1 [ng/ml]

^5^Urine (3 mL) and blood (1.5 mL) (EDTA anti-coagulated) will be collected for nuclear magnetic resonance (NMR)-based metabolome analysis

^6^Full variable of CPET consisting of forced vital capacity [L], maximal voluntary ventilation [L/min], forced expiratory volume in 1 s, one-second capacity [L], relative one-second capacity, Tiffeneau index [%], pmax [watt], HR [beats/minute], BP [mmHg], O2 saturation [%], breathing reserve [%], ventilatory threshold 1 [ml/min], ventilatory threshold 2 [ml/min], max O2 pulse [ml/beat], ventilatory equivalent for carbon dioxide slope, partial pressure in the arterial blood [mmHg], O2 partial pressure in the arterial blood [mmHg], dead space volume/tidal volume, P(A-a)O2, oxygen consumption/work load, respiratory exchange ratio (RER), pH value, PAO2 [mmHg], SaO2 [%], PCO2 [mmHg], BE [mmol/l], HCO3 [mmol/l], and SBCe [mmol/l]

^7^To be filled out by patient: EORTC-QLQ-C30—lung cancer specific LC13 and Functional Assessment of Cancer Therapy-Fatigue Scale

^8^Adverse events/serious adverse will be collected throughout the study. AEs are documented weekly by the treating physician, exercise therapist, or the study nurse using the manual of Common Terminology Criteria for Adverse Events (CTCAE) v5.0 and CTCAE after the cardio-oncology guidelines. All adverse events will be documented weekly, whereas any serious adverse event will be reported immediately (within 24 h) to the principal investigator, forwarded to the Ethics Committee and the Trial Steering Committee according to institutional requirements, collected irrespective of relatedness to exercise, and followed by appropriate clinical management by the treating team

Tobacco use plays a major role in the development of lung tumors and poorer cardiopulmonary performance. To fully understand this variable, the following items are asked: pack years and current smoking status (current smoker, non-smoker, and former smoker). A former smoker is defined as a person who has quit smoking for longer than the last 12 months. To capture this category, the abstinence date is also queried. The dose of cigarettes smoked is categorized as light smoker (persons who smoke a low number of cigarettes per day, typically less than 10 cigarettes), moderate smoker (persons who smoke a moderate number of cigarettes per day, typically between 10 and 20 cigarettes), and heavy smoker (persons who smoke a high number of cigarettes per day, typically more than 20 cigarettes).

In general, a comparison for all primary and secondary outcomes will be conducted between both exercise arms and the control arm and additionally between the two exercise arms (either t_2_ compared to t_1_ or t_1_ compared to t_0_, depending on the randomization arm).

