A pulse oximeter is employed for measuring heart rate and oxygen saturation to ensure safety. Additionally, the Borg-CR scale is utilized to assess subjective dyspnea after every second interval, providing a qualitative measure of perceived exertion and discomfort. Termination criteria are established to guide the conditions for stopping exercise within treatment arms: oxygen saturation <85% without increase during recovery and subjective increase in Borg-CR scale indicating severe dyspnea.

The control group receives a one-time physical activity consultation with general information about daily activities and exercise participation, as well as individual training recommendations. After 12 weeks, the control group will be randomized into one of the exercise groups.

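### The exercise-versus-control comparison of non-serious adverse events from t0 to t1 is open to detection bias, because one of the permitted recorders sees the exercise arms far more often

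*Protocol article*

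**What the plan says.** The abstract lists AEs among the secondary outcomes: "Secondary outcomes include quality of life, fatigue, adherence to exercise, and adverse events". The section on variables and data collection adds that "a comparison for all primary and secondary outcomes will be conducted between both exercise arms and the control arm".

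Table 2, footnote 8 governs collection. It says that "AEs are documented weekly by the treating physician, exercise therapist, or the study nurse" and then, without distinguishing arms, "All adverse events will be documented weekly". Serious events go to the principal investigator within 24 hours, whether or not they are related to exercise.

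Contact with exercise staff differs by arm. Under Methods and design, "Both intervention groups will exercise supervised twice a week for 12 weeks". Under Interventions, "The control group receives a one-time physical activity consultation with general information about daily activities and exercise participation". That section also provides for pulse oximetry and for a Borg dyspnea rating after every second interval. The other routine contact described applies to all arms. It is given in Table 2, footnote 4: "Blood sampling will be done at every visit for anti-cancer treatment mostly every 3 weeks until the study ends". The same footnote gives cisplatin regimens an additional day-8 visit.

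Under Randomization, participants are unblinded, and assessor blinding is stated only for VO2 peak testing.

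**The concern.** A fair comparison of event counts needs events to be looked for equally hard in every arm. Here one of the three permitted recorders meets exercise patients twice a week and takes physiological readings while they exert themselves. No matching observation of controls is described. Low-grade or brief events, dyspnea and desaturation in particular, can then be entered more often under exercise even if exercise does not cause them.

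At stake is the safety message for a multimorbid population. An excess of non-serious AEs under exercise could be harm, closer observation, or both. Without a record of where each event was picked up, the analysis could not tell these apart. This has to be captured prospectively, because an analysis plan cannot supply it afterwards.

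**Working it through.** **Inputs from the protocol.** Supervised sessions: 2 per week for 12 weeks. Control: 1 consultation. Anti-cancer visits: mostly every 3 weeks, in all arms. Adherence threshold: 75% of sessions. Planned size: 52 control versus 26 + 26 = 52 exercise. The protocol gives no AE rate and no detection rate, so there is no AE figure to reproduce. The group size does reproduce: 41 evaluable per group and 20% dropout give 41/0.8 = 51.25, rounded up to 52.

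**Step 1: contacts from t0 to t1, leaving aside the assessments shared by all arms.**
- Exercise: 2 × 12 = 24 sessions, plus 12/3 = 4 treatment visits, about 28.
- Control: 1 consultation, plus 4 treatment visits, about 5.
- A patient just meeting the adherence threshold still attends 0.75 × 24 = 18 sessions.
- Day-8 cisplatin visits would add contacts in every arm, so they do not close the gap.

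**Step 2: does the weekly rule remove the imbalance?** If it is fully met, each arm has 12 weekly entries. In the exercise arms an entry can rest on two directly observed sessions with oximetry and dyspnea ratings. In controls it rests on whatever enquiry the physician or nurse makes. Equal frequency of entries is not equal intensity of observation.

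**Step 3: what a detection gap would do (illustration; detection and risk values are assumed).** Observed risk = true risk × detection probability, with the same true risk in both groups. Detection is 95% under exercise. The spurious risk difference is true risk × (0.95 − control detection). The chance of p < 0.05 uses a two-sided test with 52 per group: Φ[(RD − 1.96 × SE0)/SE1], where SE0 is the pooled and SE1 the unpooled standard error.

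Worked case, true risk 50% and control detection 75%: observed risks 0.475 and 0.375, RD = 0.10. SE0 = √(2 × 0.425 × 0.575/52) = 0.0969. SE1 = √[(0.475 × 0.525 + 0.375 × 0.625)/52] = 0.0965. Then (0.10 − 1.96 × 0.0969)/0.0965 = −0.93, and Φ(−0.93) is about 0.175.

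| True risk | Control detection | Spurious RD (points) | Chance of p < 0.05 |
|---|---|---|---|
| 30% | 85% / 75% / 60% | 3 / 6 / 10.5 | 5% / 10% / 24% |
| 50% | 85% / 75% / 60% | 5 / 10 / 17.5 | 7% / 18% / 45% |
| 70% | 85% / 75% / 60% | 7 / 14 / 24.5 | 11% / 31% / 71% |

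A 10-point detection gap does little. A 35-point gap matters. The protocol does not say which is nearer the truth.

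**The case against.** The strongest reply is that the protocol requires weekly documentation for everyone and names two recorders who are not tied to the exercise sessions. This article condenses a fuller protocol, and the Table 2 schedule itself is not reproduced in the text available, so the means of weekly contact with controls may be set out elsewhere. That stands: the absence of a described call or diary is not counted as a defect.

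It also rules out a stronger reading. A reader might infer that controls are asked about AEs only every 3 weeks. For a 7-day event that gives detection of 7/21 = 33% without recall, or 0.33 + 0.67 × 0.8 = 87% if 80% of the remainder is recalled, hence an apparent rate ratio of 1.15 to 3.0 (1/0.87 to 1/0.33) if exercise detection is complete. The 3-week figure comes from the blood-sampling footnote, however, not from the AE rule. With the stated weekly interval the same formula gives 7/7 = 100% and a ratio of 1.0. Nor do controls meet study staff only once, since they attend the t0 and t1 assessments and their treatment visits. The protocol does not say who gives the consultation.

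Two further points stand. Unequal contact is inherent in supervised exercise against usual care. All secondary analyses are declared exploratory. Neither makes the observation equal, and the comparison is still planned and will be read as safety evidence.

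**Conclusion.** The concern holds in a limited form. The t0 to t1 comparison of non-serious AEs between exercise and control is open to detection bias, probably towards over-counting under exercise. This rests on three stated facts: the exercise therapist may be the recorder, contact with exercise staff is about 24 sessions against one consultation, and AEs are compared between these groups. The size cannot be derived from the document. The 3 to 24.5 points above depend wholly on assumed detection and risk values.

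The text does not show that the comparison is in fact biased, that it is uninterpretable, or that a false harm signal is likely. Serious AEs are less exposed because of the 24-hour reporting rule. Arms A and B have the same session frequency, and controls receive the same contact after crossover. The primary endpoint and the sample size are untouched.

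**What to change.** 1. Add a CRF field for the source of each AE: treatment visit, exercise session, nurse, or other contact.
2. Use the same CTCAE checklist for the weekly enquiry in all arms.
3. Report the t0 to t1 exercise-versus-control comparison twice: for all AEs, and for AEs elicited through contacts common to all arms. Tabulate session-only events separately by arm.

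The dual presentation is preferable to restricting the comparison to treatment visits. That restriction would give up the weekly interval and remove from the comparison the in-session harms most relevant to exercise safety.

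The cost is one CRF field and one extra table, with no added visits or staff. The 25 patients enrolled by 27 August 2025 will have source missing or need retrospective coding. On the planned 104, the remaining 104 − 25 = 79 could be recorded prospectively if the change had been made at that date, and fewer the later it comes.
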